### Pharmacokinetics

Pharmacokinetics of metformin are monitored to evaluate a relationship between drug exposure, toxicity, and/or efficacy. Blood samples will be taken at several time points during the study for the determination of the respective plasma levels. The half-life of metformin is ±6 h [31], which means that with daily dosing the plasma level of metformin reaches a steady-state concentration within two days. Pre-dose plasma samples (i.e. prior to study medication ingestion) will be taken on day 43 (after 6 weeks) and day 92 (after 3 months). Patients will collect their urine during 12 h on day 42 and day 91, of which a sample will be taken in which the metformin level will be determined.

### Statistical methods

The patient sample size in the clinical trial (*n* = 49) is based on a two-part trial design:
Part 1: Initially, 13 patients will be treated. If no responses are seen in the first 13 consecutive, evaluable patients, the probability of a response rate of ≥30% in the overall NMIBC patient population is < 1% (type II error) and the trial shall be terminated.Part 2: If one or more responses are seen in the first part, the study will continue until the enrolment of 49 evaluable patients is met. This allows to establish a response rate of 50% with a power of 80%, an α error of 5%, and to reject with the same power a response rate of < 30%.

According to statistical review, the analysis after part 1 is not an interim analysis and additional correction is not necessary. For the secondary endpoint concerning partial responses, the tumour dimensions captured by decentralised measurements from cystoscopy images before and after the metformin treatment will be compared using the paired samples *t*-test.

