#### Secondary objectives

To determine the partial response rate following administration of oral metformin for 3 months in a marker tumour deliberately left following transurethral resection of NMIBC lesion(s);To determine the time to recurrence;The safety of metformin in this population;Quality of life during metformin treatment using two questionnaires (SF-36 and EORTC NMIBC-24).

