### Trial end points

#### Primary end points (outcomes)

The primary outcome is the complete response rate after 3 months of treatment with metformin. Evaluable patients are those who have received at least 500 mg metformin twice daily for one week and who undergo a cystoscopy for marker lesion removal. Primary study parameters are:
Complete response: complete disappearance of the marker lesion, as confirmed by negative biopsy at the marker lesion site, the absence of new tumours at other sites and a negative bladder washout cytology;No response: marker lesion persistence or the appearance of new lesions with stage T1 or less.

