#### Secondary end points (outcomes)

The partial response rate is determined by the proportion of patients that have a ≥ 30% decrease of the sum of the longest perpendicular marker lesion diameters;The duration of the time to recurrence of NMIBC, in which patients who have continued metformin treatment after the study will be compared to those who did not. Patients will be followed for a maximum duration of 5 years. In case of a complete response; the time to recurrence is the duration of the complete response. In case of a partial response, no response or progressive disease, this is the time to recurrence after resection of the marker lesion;The number of grade 1–4 and grade 5 (fatal) NCI Common Terminology Criteria for Adverse Events Version 4.03 (CTCAE) events during treatment with metformin. All patients will be evaluable for toxicity from the time of their first treatment with metformin.

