### Therapy response assessment

The cystoscopic assessment of marker lesions is generally considered to be relatively insensitive to inter- and intra-observer heterogeneity. However, in order to pursue the most unbiased and reproducible analysis possible, cystoscopic video images of the marker lesion before and after metformin treatment will be stored and independently scored by three independent urologists that are blinded to the timing of the image acquisition (pre- or post-treatment). Differences in opinion will be discussed and, if necessary, solved by a fourth independent urologist. The urologist will judge whether there is a complete response (disappearance of the marker lesion), partial response (at least a 30% decrease of the sum of the longest perpendicular marker lesion diameters) or no response. Partial responses will be determined using the 8-mm span of the cutting loop for reference. We will perform immunohistochemical staining of tumour biology markers such as AMPK and TSC2 to investigate the molecular response of the marker lesion to metformin.

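### The partial response endpoint is a proportion, but the only analysis named for it is a paired t-test of tumour size, which does not estimate that proportion

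*Protocol article*

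**What the plan says.** Three sections of the protocol article treat partial response as a yes/no outcome per patient.

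- Secondary objectives: "To determine the partial response rate following administration of oral metformin for 3 months in a marker tumour deliberately left".
- Secondary end points: "The partial response rate is determined by the proportion of patients that have a" decrease of 30% or more in the summed diameters.
- Therapy response assessment: the urologists choose between complete response, "partial response (at least a 30% decrease of the sum of the longest perpendicular marker lesion diameters) or no response". They do so while "blinded to the timing of the image acquisition (pre- or post-treatment").

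Statistical methods then turns to a continuous outcome. Expressly for the partial response endpoint, "the tumour dimensions captured by decentralised measurements from cystoscopy images before and after the metformin treatment will be compared using the paired samples" *t*-test. No other analysis is named there for this endpoint.

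Complete response is defined more strictly under Primary end points than in the image scoring: "Complete response: complete disappearance of the marker lesion, as confirmed by negative biopsy at the marker lesion site", together with no new tumours elsewhere and negative washout cytology.

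**The concern.** The endpoint asks how many patients reached a threshold. The named test asks whether mean size changed. These can give opposite impressions, and in this trial they may well do so, because the primary endpoint is disappearance of the lesion and the design targets a 50% response rate. If vanished lesions are entered as 0 mm, they dominate the mean change. A very small p-value could then stand under the partial response heading when few or no patients had a partial response. Conversely, a modest shrinkage in everyone would be significant although nobody crossed the 30% line. In neither case would the reader get the rate that the objective promises, or its precision.

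**Working it through.** **Inputs.** From the documents: n = 49 evaluable, response rates of 30% and 50%, power 80%, α 5% (Statistical methods); marker lesion 0.5–1.0 cm (Table 1); 30% threshold (Secondary end points). Assumed here: a vanished lesion counts as 0 mm, and the size distributions stated below. The documents give no expected partial response rate.

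**The plan's own figures.** With n = 49 and success at 22 or more responses, the exact binomial gives α = 0.0195 at 30% (within one-sided 0.025) and power 0.804 at 50%. For the first part, 0.7^13 = 0.0097, below 1%. Both reproduce. The plan gives no figure for partial response.

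**Illustration by hand.** Let 24 lesions go from 7.5 mm to 0 and 25 stay unchanged.

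- Mean change = −7.5 × 24/49 = −3.67 mm.
- SD = 7.5 × √[(24/49)(25/49)(49/48)] = 3.79 mm.
- SE = 3.79/√49 = 0.541 mm.
- |t| = 3.67/0.541 = 6.8 on 48 degrees of freedom, p < 0.0001.

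The 7.5 mm cancels out of t if it is common to all lesions. Counting partial response as a category separate from complete response, the endpoint is 0/49, with exact upper 95% limit 1 − 0.025^(1/49) = 7.3%.

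**Simulation.** 5,000 runs per row, n = 49, baseline uniform 5–10 mm, non-responders with random change of SD 10%, partial responders keeping 30–70% of baseline, vanished lesions at 0.

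| True complete response | True partial response | t-test rejects | Coverage of 95% CI for mean change |
|---|---|---|---|
| 0% | 0% | 4.8% | 95.2% |
| 20% | 0% | 96.7% | 93.7% |
| 30% | 0% | 99.98% | 94.1% |
| 50% | 0% | 100% | 95.7% |
| 50% | 10% | 100% | 94.8% |
| 50% | 25% | 100% | 95.1% |

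At 50% complete response the test rejects every time whether partial response is 0%, 10% or 25%, so its result does not separate these cases. As inference on mean change it behaves acceptably.

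**Sub-threshold shrinkage.** One simulated sample in which every lesion shrinks by about 20% (SD 3 percentage points, so essentially none reaches 30%) gives |t| = 29.3 and p about 3 × 10⁻³².

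**What the proportion would deliver at n = 49** (exact 95% CI):

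| Partial responders | Rate | 95% CI |
|---|---|---|
| 0 | 0% | 0 to 7.3% |
| 5 | 10.2% | 3.4 to 22.2% |
| 10 | 20.4% | 10.2 to 34.3% |
| 15 | 30.6% | 18.3 to 45.4% |

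**Category boundaries.** Read literally, a decrease of at least 30% includes a decrease of 100%. In the illustration the rate would then be 24/49 = 49% instead of 0/49. The image scoring treats the categories as alternatives, which points to 0/49. A lesion that disappears visually but fails the biopsy, cytology or new-tumour criterion is a complete response in the image scoring and not one under Primary end points.

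**Masked reading.** For a residual lesion, 10 to 7 mm is −30% and 7 to 10 mm is +43%, yet both show a reader masked to timing the same two images. The direction can be assigned only once timing is linked, and the text does not describe that step.

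**The case against.** The best defence is that the rate can still be counted. Secondary end points says how it is determined, the urologists classify each patient, and nothing says that the *t*-test replaces the count. A condensed article may also leave the interval method to a fuller document. This stands in part: a reader might infer that the trial cannot answer its secondary objective, and that goes too far. It does not remove the mismatch, because Statistical methods does fix a method expressly for this endpoint, and that method addresses something else.

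A reader might also infer that the *t*-test is invalid because about half the post-treatment values are zero. The check does not support this: with 50% complete response, coverage of the mean change is 94.8–95.7%. Nor does the article say that vanished lesions enter the test. If only residual lesions are compared, the illustration with t = 6.8 falls away, but the mismatch and the sub-threshold example remain.

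Two further readings are too strong. One is that partial and complete response are never separated; the image scoring lists them as alternatives, so the overlap is a wording fault in Secondary end points. The other is that masking makes partial response impossible to score. Masked measurement of each image, with change derived later, fits the text; only the statement that the urologist judges the response leaves it unclear.

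Finally, change in size carries information that a 30% cut discards. That is a fair reason to keep the comparison, but as support.

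**Conclusion.** The point holds: the named analysis does not match the endpoint. It should be fixed, and it is not critical. One secondary endpoint is affected; the primary endpoint, the sample size of 49 and the first-part stopping rule are not. The fault is that mean change is a different quantity from the partial response rate, not that the test breaks down statistically. The size of the possible discrepancy (p < 0.0001 beside a rate of 0%, upper limit 7.3%) rests on two assumptions: vanished lesions count as 0 mm, and complete responders are not counted as partial responders. The simulated rejection rates also depend on the assumed lesion sizes. The mismatch itself depends on none of these.

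**What to change.** 1. In Statistical methods, make the analysis of this endpoint the partial response proportion with an exact 95% CI, on the same evaluable denominator as complete response. Report the proportion with complete or partial response beside it.
2. Align Secondary end points with Therapy response assessment so that the categories are mutually exclusive. State how a lesion that has visually disappeared but fails the biopsy, cytology or new-tumour criterion is classified. A bare rule of 30% to less than 100% would leave such a patient in neither category.
3. Keep the before-and-after size comparison as supportive only, and state whether vanished lesions are included.
4. In Therapy response assessment, say that readers masked to timing record lesion presence and diameters for each image, and that the response category is derived after timing is linked.

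The cost is wording. The same images and measurements are used, and no patient numbers or visits change.

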### Data management, auditing and access

Source data from the trial will be locally stored and entered in electronic case report forms. Based on the guidelines by the NFU (Dutch Federation of University Medical Centres) the risk of this study was qualified as ‘moderate’. According to this, a ‘minimal intensive auditing’ is advised, which will be performed by an independent clinical research associate. Besides this clinical research associate, only the investigators are allowed access to the source data. As part of informed consent, patients will be informed as to the strict confidentiality of their patient data, but their medical records may be reviewed for trial purposes by clinical research associates. This clinical trial does not have a data and safety monitoring board (DSMB).

### Informed consent

All patients will be informed by the investigator(s) concerning the aims of the study, the possible adverse events, the procedures, the possible hazards to which he/she will be exposed, who has access to their patient data and what provisions were made for compensating those who suffer harm from trial participation. It will be emphasised that the participation is voluntary and that the patient is allowed to refuse further participation in the protocol whenever he/she wants. Refusing study participation will not influence the patient’s subsequent regular medical care. Documented informed consent must be obtained for all patients included in the study before they are enrolled in the study.

### Harms

(Serious) adverse events and (serious) adverse drug reactions will be collected and recorded throughout the study period, starting at the first day of treatment through 1 month after the last dose of investigational product in accordance with Good Clinical Practice guidelines as described by the International Conference on Harmonisation (ICH-GCP). It will be left to the investigator’s clinical judgment to determine whether an adverse event is related to study treatment and of sufficient severity to require the subject’s removal from treatment or from the study. A subject may also voluntarily withdraw from treatment.

### Economic evaluation

The need for invasive treatment (with BCG or mitomycin C) and life-long surveillance (with a cystoscopy every 3 to 12 months) puts NMIBC among the most expensive cancers to treat on a per-patient basis and it represents a major public health challenge. This is augmented because NMIBC is a common cancer. Of note, metformin is off patent and, therefore, inexpensive: one year treatment of metformin 3000 mg per day costs €20.25 in the Netherlands. In this preliminary economic evaluation, we discriminate between two scenarios that do not need to be mutually exclusive:
*Metformin may decrease the need for intravesical adjuvant instillations with BCG or mitomycin C.* The costs of a single dose of 40 mg mitomycin C (€164.54) and BCG (€161.21) are similar. These costs are added to the costs for the instillation procedure itself (~€1.300, source: passantentarieven Amsterdam UMC, AMC 2019). In the first year after TURB, patients with intermediate-risk NMIBC need a total of 15 intravesical instillations with BCG or mitomycin C, with a preference for BCG [4]. Thus, the total costs per patient for adjuvant treatment with BCG in the first year after TURB are ~€22,000 (15 * (€1300 + €161.21)). In the case that oral metformin maintenance therapy renders intravesical instillations with BCG obsolete in 50% of NMIBC patients (corresponding with an expected 50% response rate in this clinical trial), this will reduce the annual medical costs of adjuvant NMIBC treatment with ~€44 million (50% * 4000 * (€22,000 – €20.25) - 50% * 4000 * €20.25).*Metformin may be effective in improving local control rates and prolonging response durations of NMIBC so that extended intervals between cystoscopic surveillance become safe.* A cystoscopy costs ~€775 and if a biopsy on the outpatient clinic needs to be performed and pathologically analyzed, this costs ~€420 extra. These costs increase dramatically if a TURB needs to be performed: €5.063,20. The average interval between follow-up with cystoscopies is, approximately, six months [4]. Therefore, the total costs per patient are ~€1550 per year (2 * €775). In the case that metformin treatment can safely double the interval between cystoscopies and biopsies from every six months to every year in 50% of NMIBC patients (corresponding with an expected 50% response rate in this clinical trial), this will reduce the annual medical costs of NMIBC surveillance in the Netherlands by ~€11.6 million (50% * 32000 * (€775 – €20.25) - 50% * 32,000 * €20.25).

In view of the early stage of evidence generated in our proposed study (phase II), an economic evaluation seems rather premature. However, in case the results suggest that metformin is effective in improving local control rates and prolonging response duration of NMIBC, we will develop a preliminary economic model to estimate long-term benefits and costs associated with treatment of NMIBC.

## Discussion

The design of the study protocol we present here comes with several strengths; To the best of our knowledge, this is the first clinical trial that investigates the treatment of non-muscle invasive bladder cancer with oral metformin. The marker lesion procedure allows intra-patient assessment of tumour response to metformin before exposing patients to this new treatment modality in a large phase 3 study. Some limitations of the study design are; the fact that the marker lesion procedure may be a hurdle for rapid patient inclusion. The ideal application of metformin in non-muscle invasive bladder cancer may not be in ablating lesions but in chemoprevention of recurrences, a treatment indication for which a marker lesion study is not the appropriate design. In non-muscle invasive bladder cancer, chemoprevention rather than chemoresection is sought for as replacement of the current standard of bladder installations with chemotherapeutic drugs of BCG.

Overall there is a solid foundation of preclinical studies that warrants a clinical trial to explore the potential role of metformin in the management of NMIBC.

If positive, this phase II trial could legitimate phase III trials in intermediate- and possibly even high-risk NMIBC patients. In the best-case scenario, these trials will show that adjuvant metformin is more effective than adjuvant BCG/mitomycin and will, therefore, render intravesical BCG/mitomycin treatment obsolete (economic evaluation, scenario 1) and also extend the safe interval between cystoscopic surveillance (economic evaluation, scenario 2), in which case the potential savings can be added. In other scenarios, metformin may be non-inferior to BCG/mitomycin, but extending the interval between cystoscopic surveillance may not be safe. In that case, only the savings from scenario 1 apply. In brief, the nature of the proposed oral metformin treatment offers various cost-saving opportunities compared with the current standard of care for NMIBC.

## Data Availability

Data sharing is not applicable to this article as no datasets were generated or analysed during the current study.

## Abbreviations

AMPK: Adenosine monophosphate kinase
b.i.d.: Bis in die, two times a day
BCG: Bacillus Calmette-Guérin
CCMO: Dutch national competent authority
CTCAE: Common Terminology Criteria for Adverse Events
ETC: Electron transport chain
ICH-GCP: International Conference on Harmonisation – Good Clinical Practica
NMIBC: Non-muscle-invasive bladder cancer
q.d.: Quaque die, one a day
T2DM: Diabetes mellitus type II
TCA cycle: Tricarboxylic acid cycle
TSC2: Tuberous sclerosis complex 2
TURB: Transurethral resection of the bladder
